### Combined treatment

All participants will receive conventional therapy in the same way. This is defined as general neurosurgical management carried out in SAH patients to stabilize the vital signs, control pain, and prevent vasospasm through fluid or medication therapy. Any use of medication will be recorded on the case report forms every day.

### Dropout criteria

Participants conforming to any of following conditions will be removed from the study: (1) more than three sessions (out of a total of 12) are not performed; (2) withdrawal of patient consent; (3) severe adverse events making the trial unsustainable; (4) worsening condition making it difficult to participate in the trial; or (5) impractical to continue with the trial, as judged by the principal investigator.

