### Outcome measures

#### Primary outcome measurement

The occurrence of DIND will be compared between the study group and the control group. DIND is defined as an unaccountable new focal neurological deficit lasting ≥2 h. Any occurrence of DIND will be recorded by the physician and verified by the investigator every day.

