### Safety evaluation

Any adverse events or abnormalities will be recorded in the case report forms irrespective of the intervention used. Severity will be evaluated as mild, moderate, or severe, and the relation of any events to the intervention will be evaluated as not related, possibly related, or related.

If any serious adverse events occur, the intervention will be stopped immediately and appropriate action will be taken. This will be reported promptly to the institutional review board, according to the protocol.

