### Sample size estimation

DIND, the primary outcome of the trial, was used to calculate the sample size. According to our pilot trial carried out in 2012, the incidence rate of DIND was 10% in the study group and 38.9% in the control group [24]. The difference in the expected incidence rate of DIND between the two groups (P_c_ - P_t_) is therefore 28.9%. To detect this difference with a two-sided 5% significance level and a power of 95%, 39 participants per intervention arm have to be randomized, allowing for a 20% dropout rate [31].$$ n=\frac{{\left({z}_{\alpha /2}+{z}_{\beta}\right)}^2\left({p}_c{q}_c+{p}_t{q}_t\right)}{{\left({p}_c-{p}_t\right)}^2} $$

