### Statistical analyses

According to the principle of intention-to-treat, all randomized participants will be analyzed using SPSS version 18.0 (SPSS Inc., Chicago, IL, USA) software. All data will be represented as mean ± standard deviation (SD) or number (%). For comparisons of two groups, an independent samples *t*-test or Mann- Whitney *U* test will be used for continuous outcomes, and a χ^2^-test or Fisher’s exact test will be used for noncontinuous outcomes. To control for possible confounding factors (for example, age, Hunt and Hess Scale, modified Rankin Scale, *etcetera*), multiple regression analysis will be performed for the comparison of two groups. Confidence limits of 95% will be calculated and *P* values of < 0.05 will be considered statistically significant.

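### The dropout criteria take patients out of the study, not only off the intervention, for reasons related to the outcome; this conflicts with the intention-to-treat analysis of all randomized patients.

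*Protocol article*

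**What the plan says.** The protocol's Dropout criteria section states that "Participants conforming to any of following conditions will be removed from the study". It lists five conditions:

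1. "more than three sessions (out of a total of 12) are not performed";
2. withdrawal of consent;
3. "severe adverse events making the trial unsustainable";
4. "worsening condition making it difficult to participate in the trial";
5. a judgement by the principal investigator that continuing is impractical.

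The Statistical analyses section states: "According to the principle of intention-to-treat, all randomized participants will be analyzed".

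Three other sections bear on the point. Safety evaluation says: "If any serious adverse events occur, the intervention will be stopped immediately and appropriate action will be taken". Sample size estimation enlarges the trial by "allowing for a 20% dropout rate". Primary outcome measurement says: "DIND is defined as an unaccountable new focal neurological deficit lasting ≥2 h", and has its occurrence recorded and verified daily. Under Assessment and Secondary outcome measurements, mRS and mortality are planned at the end of treatment and 14 days later (or at discharge).

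**The concern.** An intention-to-treat analysis needs outcome data on every randomized patient, whatever happened to treatment. Of the five criteria, only withdrawal of consent is a natural reason to stop collecting data. The other four are events or judgements after randomization, and here they are not independent of the outcome. The primary outcome is a new neurological deficit, so it can be the very worsening that leads to removal.

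Removal could also differ by arm. Only the study group receives penetrating needles and current, and the treating practitioner is not listed among those blinded. If patients at higher risk leave observation, the comparison of DIND, mRS and mortality no longer rests fully on the randomized groups. Equal loss in both arms costs power, and unequal loss can bias the result in either direction. An analysis plan cannot recover observations that the protocol has stopped collecting.

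**Working it through.** **1. The sections side by side.** Dropout criteria ends participation in the study. Statistical analyses includes all randomized participants. No section says that a removed patient is still observed for DIND, mRS or death, or how that patient enters the analysis. The 20% dropout allowance points the same way, since enlarging the sample for dropout treats dropouts as lost to the analysis.

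**2. How removal can follow from a treatment stop.** Criterion 1 is met when fewer than 9 of the 12 sessions are given. If the intervention stops for good at or before session 8, at least 12 − 8 = 4 sessions are missed, so the patient meets criterion 1. A stop under Safety evaluation can therefore become removal from the study.

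Timing: assume one rest day after each six sessions. Session 9 then falls 9 days after session 1, which is day 10 to 13 after hemorrhage for a start on day 1 to 4. The Background puts the peak of vasospasm at days 7 to 10. A permanent stop during the peak would nearly always leave fewer than 9 sessions given.

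**3. The plan's own sample size.** Inputs from Sample size estimation: p_c = 0.389, p_t = 0.10, two-sided 5%, power 95%, 20% dropout. The protocol's formula is n = (z_{α/2} + z_β)²(p_c q_c + p_t q_t)/(p_c − p_t)².

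- At 95% power: (1.960 + 1.645)² × 0.3277 / 0.289² = 51.0 per arm; with 20% dropout, 51/0.8, so 64.
- At 80% power: (1.960 + 0.842)² × 0.3277 / 0.289² = 30.8, so 31 per arm; with dropout, 31/0.8, so 39.

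The stated 39 matches 80% power, not 95%. That is a separate matter, but it explains why the baseline below is not 95%.

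**4. Illustration: equal loss in both arms.** The protocol plans 80 patients; I take 40 per arm. Expected DIND events are 40 × 0.389 + 40 × 0.10 = 15.6 + 4.0 = 19.6. Let f be the fraction of DIND patients removed without the event being counted. **f is an assumption; the protocol gives no value.** The observed rate is p(1 − f)/(1 − pf) on 40(1 − pf) patients. Power = Φ(difference/SE − 1.96), with unpooled SE as in the protocol's formula.

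| f | Control | Study | Difference (points) | Patients left | Power, unpooled | Power, pooled |
|---|---|---|---|---|---|---|
| 0 | 38.9% | 10.0% | 28.9 | 40.0 / 40.0 | 89% | 87% |
| 10% | 36.4% | 9.1% | 27.3 | 38.4 / 39.6 | 86% | 84% |
| 25% | 32.3% | 7.7% | 24.6 | 36.1 / 39.0 | 79% | 77% |
| 50% | 24.1% | 5.3% | 18.9 | 32.2 / 38.0 | 62% | 62% |

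**5. Illustration: loss in the study arm only, no true effect.** The true rate is 38.9% in both arms.

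- f = 25%: observed 38.9% v 32.3%; two-sided type I error 9% by either test.
- f = 50%: observed 38.9% v 24.1%; two-sided type I error 26% (pooled) to 28% (unpooled).

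**The case against.** The best defence is that the text claims less than a hasty reader may infer. Much of it stands.

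- **That every patient who worsens or has a severe adverse event is removed.** The protocol does not say this. Criteria 3 and 4 carry qualifiers, and a patient with DIND who can still receive sessions does not meet criterion 4.
- **That the rule deletes the patients having the primary event.** This is not shown. DIND is recorded daily, and no section discards data obtained before removal. A DIND that leads to removal could already be on record. The protocol does not say that it counts, so the question is open.
- **That intention-to-treat is impossible.** This goes too far. The sections planning mRS and mortality exclude no one, and follow-up after removal is neither promised nor denied.
- **That every DIND stops treatment under Safety evaluation.** This would need DIND to be classed as a serious adverse event, which the protocol never states.
- **That the 16 allowed dropouts (20% of 80) are largely the roughly 20 expected DIND patients.** Nothing supports this. The allowance covers all causes, including withdrawn consent.

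Condensation into an article may explain some silence on follow-up. It does not explain the conflict, because the article states both rules outright. On the wording as it stands, events after removal are still lost.

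**Conclusion.** The point holds as a contradiction with consequences for the data. Removal from the study under criteria 1, 3, 4 and 5 cannot be squared with analysing all randomized patients unless follow-up continues, and the protocol does not say that it does. Read as written, DIND arising after removal and later mRS and mortality are not collected, for reasons related to the outcome.

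The size of the effect is unknown. The figures in the working depend on the assumed fraction f, on 40 patients per arm, on the protocol's own event rates and on normal-approximation tests. They are a sensitivity range, not an estimate. They show that a modest loss, equal in both arms, costs little power (89% to 86% at f = 10%), while a large or one-sided loss would matter. Confidence is high on the conflict and low on how many primary events would actually go uncounted. It should be settled in the protocol, because the missing observations cannot be recovered afterwards.

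**What to change.** Reconcile Dropout criteria, Safety evaluation and Statistical analyses by separating stopping the intervention from leaving the study:

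- Keep whatever stopping rules the sponsor chooses, but under criteria 1, 3, 4 and 5 let them end the intervention only. No view is taken here on when treatment should stop.
- Follow every randomized patient for DIND to the end of the 2-week period, and for mRS and mortality at the planned follow-up. The only exception is a patient who refuses further data collection.
- State that any DIND or death before or at the stop counts as an event.
- Analyse all patients by randomized arm.

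The cost is a change of wording and continued recording, in patients who will mostly still be in hospital.

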### Outcome measures

#### Primary outcome measurement

The occurrence of DIND will be compared between the study group and the control group. DIND is defined as an unaccountable new focal neurological deficit lasting ≥2 h. Any occurrence of DIND will be recorded by the physician and verified by the investigator every day.

#### Secondary outcome measurements

Secondary outcome measures are as follow:Incidence of angiographic vasospasmAngiographic vasospasm is defined as focal or generalized reduction of cerebral arterial caliber on conventional cerebral angiogram or CT angiography confirmed by a neuroradiologist and a neurosurgeon.Incidence of TCD vasospasmTCD vasospasm is defined as a peak systolic middle cerebral artery velocity (PCA_MCA_) of >200 cm/s and a Lindegaard ratio of >3 (Lindegaard ratio = mean velocity in the MCA/mean velocity in the ipsilateral extracranial internal carotid artery) [28-30].Incidence of vasospasm-related infarct on CT or MRIA vasospasm-related infarct is defined as a cerebral infarction in the region of angiographic vasospasm or TCD vasospasm as shown on CT or MRI.Changes in plasma NO and endothelin-1A blood sample (3 mL) will be taken from the brachial vein, centrifuged at 3,000 rpm for 15 min, and kept in a freezer at -70°C before analysis. The concentration of NO will be analyzed using a Total Nitric Oxide and Nitrate/Nitrate Parameter Assay Kit (R&D Systems, Inc., USA) and the level of endothelin-1 will be measured using an Endothelin-1 Quantikine ELISA Kit (R&D Systems, Inc., USA). All samples will be discarded after analysis (www.rndsystems.com).Mortality at the end of treatment and 14 days after treatment (or at discharge)Modified Rankin Scale (mRS) scoreFunctional status is assessed with mRS score at the end of treatment and 14 days after treatment (or at discharge).

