## Background

Subarachnoid hemorrhage (SAH) can occur spontaneously or as a result of trauma [1]. The most common cause of spontaneous SAH is aneurysm rupture (about 80% of cases), while vascular malformations, tumors, venous angioma, or infectious aneurysms may also cause bleeding [2,3]. The incidence rate is about 1 per 10,000 people per year, and SAH accounts for about 5% of stroke patients [3,4]. The rate of SAH is low when compared to cerebral hemorrhage or cerebral infarction; however, this condition is a large burden to both individual patients and society because of high mortality rates and treatment costs in neurological intensive care units [5-7].

Treatment of SAH involves early ligation of the aneurysm or insertion of a coil; however, complications such as cerebral vasospasm, rebleeding, or hydrocephalus frequently occur after successful surgery [2-4,7,8]. Such complications increase the mortality rate of SAH or lead to patient sequelae [4]. In particular, cerebral vasospasm is the most serious complication of SAH [9]. It is reported that 23% of the deaths or disabilities that occur as a result of SAH are due to vasospasm [10]. Cerebral vasospasm begins 3 to 4 days after the onset of SAH and reaches a maximum between 7 and 10 days [7,11,12]. Vasospasm occurs in 50 to 70% of SAH patients, and about 50% of these patients suffer neurological symptoms such as deterioration of consciousness and language disorders [3,11,13]. Such symptoms are known as delayed ischemic neurological deficit (DIND). Cerebral infarction occurs in half of DIND patients and a permanent neurological deficit remains in about 35%. In addition, 30% of patients die of DIND [4,7].

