Spontaneous vasoconstriction and vasodilatation are adjusted by the physiological regulation of vascular endothelial cells [14]. If a cerebral aneurysm ruptures and cerebral blood flow enters the subarachnoid space, hemoglobin in the blood increases the production of reactive oxygen species (ROS) [15]. This triggers secretion of the vasoconstrictor substances endothelin-1, prostaglandin H2, and thromboxane A2 from vascular endothelial cells and decreases levels of the vasodilatory substance nitric oxide (NO) [6,9,10,15,16]. It is known that cerebral vasospasm occurs via this mechanism. In particular, NO and hemoglobin combine very easily; thus, the presence of hemoglobin results in the loss of vasodilatory function [16]. To prevent vasospasm on the basis of its pathogenesis, various methods such as calcium channel blockers, magnesium sulfate, statin agents, endothelin antagonists, and nicardipine prolonged release implants have been used [2,3,7]. However, their effects are limited and various studies of new drugs and treatments are now under way [4,9,10].

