### Intervention

Intervention will start within 96 h of SAH, after ruptured aneurysms have been secured by endovascular coiling or surgical clipping. Interventions will be applied once a day, 6 days a week for 2 weeks (a total of 12 sessions) in addition to standard treatments such as prophylactic hypertensive, hypervolemic, and hemodilution (triple-H) therapy and nimodipine. Sterile disposable stainless steel acupuncture needles (length, 4 cm; diameter, 0.25 mm) will be used. All interventions will be performed by one Korean Medicine doctor with over 3 years of working experience who completed a college education of 6 years. This doctor will be trained in the study protocol before the start of the trial.

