### Assessment

The evaluation of each assessment scale will be performed by an investigator blinded to the assigned group. A baseline assessment will include Fisher grade (FG), HHS, modified Rankin Scale (mRS), NO and endothelin-1 in plasma [26]. The occurrence of delayed ischemic neurological deficit (DIND), TCD vasospasm, angiographic vasospasm and a vasospasm-related cerebral infarction will be monitored during the study period. DIND is defined as an unaccountable new focal neurological deficit lasting >2 hours with either angiography or transcranial Doppler findings [27]. TCD (Transcranial Doppler Sys, 2-channel, DWL, Germany) monitoring will be done by a skilled researcher at a certain time every other day [8]. CT angiography or conventional cerebral angiography will be performed when an abnormal increase in blood flow velocity is shown or any neurological changes occur [4,10]. If necessary, we will check whether vasospasm-related infarction has occurred using CT or magnetic resonance imaging (MRI) [8]. Modified Rankin scale will be measured after 2 weeks, and the follow-up assessment will be conducted 2 weeks after the primary endpoint in order to evaluate mortality and mRS.

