## Discussion

In this randomized controlled trial, we aim to observe the effect of acupuncture treatment on the prevention of vasospasm after SAH. In addition to the occurrence of DIND and vasospasm, plasma levels of NO and endothelin-1 will be evaluated to identify the mechanism of action of the treatments used. Stratified block randomization will be used according to sex and severity (HHS). For the placebo control, we will use an electric stimulator without electrical flow and sham intradermal acupuncture designed not to penetrate the skin. With use of the same electrical stimulator and intradermal acupuncture method as the treatment group, better blinding of the control group is expected. Participants will be treated alone in a treatment room in order to avoid any communication with other participants.

In summary, the effect of acupuncture treatment on the prevention of vasospasm after SAH will be assessed in this trial. The placebo effect should be excluded and the trial design should allow for evaluation of the efficacy and safety of acupuncture for SAH patients.

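### The biomarker outcome is a change score, and the named regression covariates omit the baseline biomarker and time since haemorrhage: a minor loss of precision, not a bias

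*Protocol article*

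**What the plan says.** The protocol article lists the biomarkers under Secondary outcome measurements: "Changes in plasma NO and endothelin-1A blood sample (3 mL) will be taken from the brachial vein". The title of the item ends at endothelin-1 and the sampling sentence follows on, so the outcome is named as a change. The Discussion gives its purpose: "plasma levels of NO and endothelin-1 will be evaluated to identify the mechanism of action of the treatments used".

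The Assessment section puts both markers at baseline: "A baseline assessment will include Fisher grade (FG), HHS, modified Rankin Scale (mRS), NO and endothelin-1 in plasma". The text fixes no hour after SAH for that sample. The Intervention section sets only the start of treatment: "Intervention will start within 96 h of SAH, after ruptured aneurysms have been secured by endovascular coiling or surgical clipping".

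Under Statistical analyses, an independent samples t-test or Mann-Whitney U "test will be used for continuous outcomes". The same section adds a multiple regression for the group comparison to control for possible confounders. Age, Hunt and Hess Scale and modified Rankin Scale are given as examples, and the list is left open with an etcetera. Randomization is stratified by sex and Hunt and Hess Scale.

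**The concern.** The Background says that the bleed itself releases endothelin-1 and lowers NO, and gives a time course for its consequence: "Cerebral vasospasm begins 3 to 4 days after the onset of SAH and reaches a maximum between 7 and 10 days". If treatment can start at any point up to 96 h, the baseline sample can fall at different stages of that process. One patient's change then starts early in the natural course and another's starts on day 4.

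A change score subtracts the whole of each baseline value, including the part that reflects only when the sample was drawn. When baseline and follow-up are weakly correlated, this adds noise instead of removing it. These two markers are the trial's only direct evidence on mechanism, and there are about 40 patients per arm at most. Precision that could be had from data already collected is worth having.

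**Working it through.** **Inputs.** The total is 80 patients, taken as 40 per arm (1:1 is assumed; the sample size section also counts equal arms). The documents give no SD, correlation or time trend for NO or endothelin-1, so r and the drift below are assumed and shown as ranges. There is no plan figure to reproduce: the only computed figure is the sample size for delayed ischemic neurological deficit, which does not concern the biomarkers.

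**1. Change score against baseline adjustment.** Let both measurements have SD s and correlation r. The per-patient variances are:

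- change: 2s²(1−r)
- follow-up value alone: s²
- follow-up value adjusted for baseline: s²(1−r²)

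The ratio of adjusted to change is (1−r²)/[2(1−r)] = (1+r)/2. The ratio of change to follow-up alone is 2(1−r).

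| r | adjusted / change | change / follow-up alone | adjusted / follow-up alone |
|---|---|---|---|
| 0.2 | 0.60 | 1.6 | 0.96 |
| 0.3 | 0.65 | 1.4 | 0.91 |
| 0.5 | 0.75 | 1.0 | 0.75 |
| 0.7 | 0.85 | 0.6 | 0.51 |

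At r = 0.3 the gain equals 1/0.65 = 1.54 times as many patients for this comparison. Below r = 0.5 the change score is noisier than ignoring baseline; above it, the change score does better than the follow-up value alone.

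Equal variances are not essential to the direction. With SDs sX (baseline) and sY (follow-up), the change variance minus the adjusted variance is (sX² + sY² − 2r·sX·sY) − sY²(1−r²) = (sX − r·sY)², which is never negative. In large samples, adjustment therefore cannot lose.

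**2. Detectable difference.** At two-sided 5% and 80% power (a conventional reference point, not the plan's) this is (1.960 + 0.842)·√(2/40) = 0.626, multiplied by the SD of the quantity analysed:

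| r | change score | baseline-adjusted |
|---|---|---|
| 0.3 | 0.74 SD | 0.60 SD |
| 0.5 | 0.63 SD | 0.54 SD |
| 0.7 | 0.49 SD | 0.45 SD |

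**3. Sampling time alone.** Suppose the baseline sample is drawn uniformly over 0 to 96 h and the marker drifts linearly by b SD over that window. This adds b²/12 to the variance of change (in units of s²). At r = 0.5 the variance of change without drift is 1, so the SE is multiplied by √(1 + b²/12):

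| b | variance factor | SE factor |
|---|---|---|
| 0.5 | 1.021 | 1.01 |
| 1.0 | 1.083 | 1.04 |
| 1.5 | 1.188 | 1.09 |
| 2.0 | 1.333 | 1.15 |

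Most of the loss comes from the change score itself. Timing adds little unless the drift is well over 1 SD.

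**The case against.** The strongest objection is that the plan does not rely on an unadjusted test alone. A reader who stops at the t-test might infer that it does, but the regression in the same section is not limited to particular outcomes and its covariate list is explicitly illustrative. Baseline NO, baseline endothelin-1 and time since SAH could all be added under it, and a full analysis plan may say so. This stands, and it rules out describing the comparison as simply unadjusted. It does not remove the point: nothing in the text makes a baseline-adjusted comparison the biomarker analysis, and the stated reason for the regression is confounding, not precision.

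Second, the change-score test is a reading. The outcome is titled as a change, but the analysis section does not define an end-minus-baseline variable. If follow-up values were compared directly instead, adjustment would still help, by the last column of the first table.

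Third, the 0 to 96 h window is inferred from the treatment-start rule. The flow chart is not shown and may carry sampling times. Diagnosis, securing of the aneurysm, consent and grading all come before treatment, so the earliest hours are unlikely to be used. The timing figures are therefore probably upper values for a given rate of drift.

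Fourth, a reader might infer that unequal disease stage at baseline biases the treatment contrast or invalidates the mechanism result. The documents do not support that: allocation is randomized, so time since SAH is balanced in expectation, and its variation adds noise only.

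**Conclusion.** The point holds as a minor matter of efficiency. The biomarker outcome is framed as a change, and the named covariates leave out the two that bear most directly on it. If the change score is tested as it stands, its variance exceeds that of the baseline-adjusted comparison by a factor of 2/(1+r): 1.67 at r = 0.2 falling to 1.18 at r = 0.7. This rests on equal variances, a large-sample approximation and assumed correlations. The further contribution from sampling time is modest and rests on an assumed linear drift and an inferred window. The outcome is secondary, and neither the primary comparison nor the validity of the biomarker contrast is affected.

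**What to change.** In Statistical analyses, state that the main comparison of NO and of endothelin-1 is an analysis of covariance of the follow-up value (log scale if skewed) on arm. The covariates are that marker's baseline value, on the same scale, and the hours from SAH to the baseline sample. This sits within the regression already planned; the t-test or Mann-Whitney test of change can stay as a supporting analysis. Fix the wording before unblinding, so that the open covariate list is closed for this outcome.

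The cost is a sentence of wording and two degrees of freedom. Baseline values are already collected, and the time of SAH is needed for the 96 h criterion. The only item to confirm is that the draw time of the baseline sample is recorded.

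### One section allows the second mortality and mRS assessment at discharge and another does not, so follow-up time can depend on recovery

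*Protocol article*

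**What the plan says.** Only the protocol article is at hand. It times the second assessment of mortality and mRS in two sections.

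- **Secondary outcome measurements.** The mortality entry reads "Mortality at the end of treatment and 14 days after treatment (or at discharge", where the bracket then closes. The mRS entry has the same two time points and the same bracketed alternative. Neither entry says when discharge replaces the fixed day, or whether the earlier or the later of the two dates counts.
- **Assessment.** This section first says "Modified Rankin scale will be measured after 2 weeks", and then that "the follow-up assessment will be conducted 2 weeks after the primary endpoint in order to evaluate mortality and mRS". It does not mention discharge.

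Three other sections bear on how these are read. Under Intervention, "Interventions will be applied once a day, 6 days a week for 2 weeks (a total of 12 sessions" over that period, and "Intervention will start within 96 h of SAH". Under Primary outcome measurement, "The occurrence of DIND will be compared between the study group and the control group", so the primary outcome is an event (delayed ischemic neurological deficit, DIND) and not a date.

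**The concern.** A discharge date is set after randomization and generally reflects how the patient is doing. If it can stand in for a fixed day, each patient's outcome is read at a time that partly depends on that outcome. Three things follow.

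- **Unequal stage of recovery.** If mRS is still changing in these weeks, a patient scored at discharge and one scored on the fixed day are not being compared at the same stage.
- **Uncounted deaths.** A patient assessed on leaving hospital is alive at that moment. If that closes the record, a death between discharge and the fixed day is lost from the mortality count.
- **No protection in the stated analysis.** Statistical analyses describes two-group tests plus regression on possible confounders (age, Hunt and Hess Scale and mRS are its examples). Nothing stated there deals with unequal follow-up, and no later analysis can recover an mRS score that was never taken on the common day.

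The two sections also disagree: one permits discharge as a time point and the other does not. Sites of error like this are settled patient by patient in practice, and the choice may not be the same for everyone.

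**Working it through.** The plan gives no figure on this point, so there is none to reproduce. The check sets the two sections side by side and counts days.

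**Step 1. Do the two sections name the same fixed day?** Treatment lasts two weeks (Intervention), and the first mRS after baseline is taken after two weeks (Assessment). If the primary endpoint in Assessment means the end of that period, then

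- Assessment: 14 + 14 = day 28 from the first session (first session = day 0);
- Secondary outcome measurements, fixed-day part: 14 + 14 = day 28.

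The fixed days agree. What remains is the discharge alternative, present in one section and absent from the other.

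**Step 2. The fixed schedule relative to the hemorrhage.** Treatment starts within 96 / 24 = 4 days of the hemorrhage.

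- End of treatment: 0 + 14 = day 14 to 4 + 14 = day 18.
- Follow-up: 14 + 14 = day 28 to 18 + 14 = day 32.

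This spread of up to 4 days is set by when treatment starts and does not depend on how the patient fares afterwards.

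**Step 3. What the discharge alternative does to the gap between end of treatment and assessment.** Discharge dates are not given. The lower limit below assumes that nobody leaves before treatment ends.

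| Reading of the alternative | Gap after end of treatment | Day from first session |
|---|---|---|
| Fixed day for all | 14 days | 28 |
| Earlier of the two dates | 0 to 14 days | 14 to 28 |
| Later of the two dates | 14 days or more, no upper limit | 28 or later |
| Discharge only if the patient cannot be seen on the fixed day | 14 days for those seen, the discharge date for the rest | mixed |

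At a gap of 0 the second assessment coincides with the end-of-treatment one and adds nothing. Deaths are lost after an early discharge under the earlier-date reading, and under the fallback reading for the patients who are not seen. Under the later-date reading long-stay patients are instead observed for longer than the others.

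**Step 4. When does this become bias between arms?** Only if discharge timing differs by arm. The trial's own hypothesis makes that plausible: Sample size estimation assumes that "the incidence rate of DIND was 10% in the study group and 38.9% in the control group", and Background reports a lasting deficit in about 35% of patients with DIND. If the hypothesis is true, the better arm may leave sooner. Under the earlier-date reading it is then scored with less time to recover, which would understate an mRS benefit, and its death count is cut short, which would flatter its mortality. Under the later-date reading the worse arm gets more time to recover and a longer window for deaths, so the two effects again oppose each other. The direction has to be considered outcome by outcome, and the size depends on discharge data that the document does not contain.

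**The case against.** The strongest case on the other side has five parts.

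- **The anchors do not really conflict.** A reader might infer that timing follow-up from the primary endpoint means counting from the DIND event. That is strained: patients without DIND would have no follow-up date at all, and the sentence comes straight after the two-week mRS. On the natural reading the two sections give the same fixed day. This stands, and the dependence on recovery comes from the discharge alternative alone. The phrase is still loose, because the primary outcome is an event.
- **The earlier-date reading is not stated.** A reader might infer that patients who do well are scored early and the others on the fixed day. The article does not say so; it could mean the later date or a fallback. This stands too, but each of these readings allows unequal follow-up.
- **No share of affected patients is known.** Length of stay is not given, so the number discharged before the fixed day could be small. This stands and is why no size is claimed.
- **Bias needs a difference between arms.** If acupuncture does nothing and conventional care is the same for all, as Combined treatment says, discharge timing should be similar in both arms. This is correct; the risk arises where treatment affects recovery, which is the case the trial is built to detect.
- **The article condenses a fuller protocol.** That document may contain a rule for discharge. But the article states the timing twice and differently, so this is a discrepancy in stated text, not a detail left out.

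**Conclusion.** The point holds in a limited form. The outcome list allows discharge as an alternative for the second mortality and mRS assessment without a rule for its use, and the Assessment section does not allow it. If the discharge date is used, follow-up after treatment varies by up to 14 days when the earlier date applies and without limit when the later applies, and deaths after an early discharge go uncounted. The second comparison of these two secondary outcomes may then be biased if length of stay differs by arm.

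The amount of bias cannot be computed from the document. A reader might try to put a number on the missed deaths with an assumed daily risk; at 0.5% a day, for example, 1 − 0.995^7 = 3.4% over 7 days and 1 − 0.995^14 = 6.8% over 14. The document gives no such risk. It would be applied to the very patients well enough to go home, and it describes one patient's risk, not a difference between arms. It should not be used.

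The DIND comparison, the sample size and the end-of-treatment mortality and mRS are not affected. This should be corrected, but it does not threaten the main result. The conclusion rests on two assumptions: that discharge is linked to recovery, and that the discharge option would be used for at least some patients.

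**What to change.** - In Secondary outcome measurements, delete the bracketed discharge alternative from both the mortality and the mRS entries.
- In Assessment, replace the reference to the primary endpoint with the scheduled end of treatment.
- State one day for vital status and mRS in all randomized patients: 14 days after the scheduled end of treatment, which is day 28 from the first session. The scheduled end is a better anchor than the actual one, because Safety evaluation provides for stopping the intervention early, which would otherwise move the date.
- Have the blinded assessor telephone patients who have already been discharged.

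**Cost.** One call for each discharged patient, made by someone who remains blinded, and an amendment during recruitment (Trial status gives a start in September 2014). Patients already scored at discharge cannot be given a day-28 mRS afterwards, although their vital status on that day may still be obtainable. Telephone scoring for some and bedside scoring for others would make the mode of assessment depend on recovery; using the same structured interview for everyone avoids this. A few discharged patients may be unreachable and would have missing data.
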